### **XIV. Procedure:**

Participants will be screened based on the inclusion and exclusion criteria. Individuals meeting the inclusion criteria will be recruited for the study after being informed about the purpose and nature of the study. Written informed consent will be obtained from all participants. Participants will then be randomly divided into two groups: group a and group b, with equal participants in each group.

Before the intervention, both groups will undergo baseline assessments for sprint performance and change of direction (cod) ability. Once baseline testing is completed, participants will receive their respective interventions as described below:

- Group A: Accentuated eccentric loading (AEL) countermovement jumps, drop jump training with ladder training.
- Group B: Ladder training only.

Group A will receive accentuated eccentric loading (AEL) countermovement jumps and drop jump training with ladder training and Group B will receive Ladder training.

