## **IX. Methodology:**

**Study type:** Experimental study

**Study design:** Randomised controlled trial (RCT)

**Target population:** Futsal players

**Sampling technique:** Simple random sampling

**Duration of study:** 1 year

**Allocation ratio:** 1:1

**Blinding:** Single blinded (participants will be blinded)

**Study setting :** futsal turfs across dmiher , Sawangi Meghe Wardha

**Study population:** recreational and competitive futsal players

**Sample size:** the sample size for this study was determined using g\*power (version 3.1.9.4, heinrich heine universität düsseldorf, düsseldorf, germany), a statistical software that facilitates power analysis and sample size estimation based on various statistical tests.

formula using mean difference

$$n1 = n2 = 2 \times [(z\alpha + z\beta)^2 \times \sigma^2] / (\delta^2)$$

Where:

- $Z\alpha = 1.96$  (considering ci at 95%)
- $Z\beta = 1.64$  (power at 95%)

**Primary variable:** 30 m sprint

- Mean  $\pm$  sd (pre) result on 30 m sprint in tbi readings =  $4.36 \pm 0.12$
- Mean  $\pm$  sd (post) result on 30 m sprint in tbi readings =  $4.29 \pm 0.13$
- Mean difference ( $\delta$ ) = 0.064
- Pooled standard deviation = 0.125

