### **XIII. Eligibility criteria:**

➤ **Inclusion criteria:**

- (1) Age between 18-30 years
- (2) BMI-18.5–24.9
- (3) Regular participation in futsal activities since 1 year.
- (4) Recreational and competitive futsal players participating in regional, national, or professional leagues
- (5) Willingness to participate in a structured 6-week intervention program focusing on accentuated eccentric loading  
Countermovement jumps, drop jump training, and ladder drills.

➤ **Exclusion criteria:**

- (1) presently having pain due to trauma associated to lower limb
- (2) laxity of articular ligaments or meniscus injury around knee
- (3) recent history of dislocation of patella or recent fracture
- (4) chondromalacia patella
- (5) existing progressive neurological conditions
- (6) plantar fasciitis

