### Participant timeline:

Once ethical approval is obtained from the university ethical committee, the subjects will be recruited from the RNPC Department of Sports Physiotherapy. After receiving consent from the subjects, they will be assessed and then will be divided into 2 groups.

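### No concealment of assignment is described, and the protocol contradicts itself on whether baseline testing comes before or after players are split into equal arms

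*Protocol*

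**What the plan says.** Three places in the protocol deal with assignment.

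- Section IX (Methodology) gives "Allocation ratio: 1:1". It also gives "Sampling technique: Simple random sampling", which is a label for how players are selected, not for how they are assigned.
- Section XIV (Procedure), after describing screening and consent, states: "Participants will then be randomly divided into two groups: group a and group b, with equal participants in each group". It continues: "Before the intervention, both groups will undergo baseline assessments for sprint performance and change of direction (cod) ability".
- The participant timeline states: "After receiving consent from the subjects, they will be assessed and then will be divided into 2 groups".

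The schedule in section XVII marks baseline variables in the enrolment column and allocation in the next column. The text above it also places pre-intervention data at enrolment.

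On blinding, section IX says "Single blinded (participants will be blinded" and names no one else. The visible text names no sequence generator, list holder, envelope or central assignment, and it does not separate the person who enrols from the person who assigns.

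**The concern.** Two protections are at stake.

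The first is an unprejudiced baseline. Section XI lists a stopwatch as a manual timing option, and section XVI reports only moderate reliability for manual timing (ICC 0.60 to 0.75), with error from human reaction time. A tester who already knows the arm can influence such a reading, even unintentionally. If the analysis compares changes, any average timing difference between arms at baseline passes one for one into the estimated effect. The effect planned for is 0.064 s.

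The second is unprejudiced entry. Where the next arm can be foreseen, the timing of a player's enrolment or a borderline eligibility judgement can depend on it. Group A does loaded and box jumps and Group B does ladder drills only, so staff will see past assignments. Participant blinding offers little reassurance, because an inclusion criterion tells players what the training contains: "Willingness to participate in a structured 6-week intervention program focusing on accentuated eccentric loading". Concealed assignment is therefore the main safeguard left, and it cannot be restored after enrolment.

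**Working it through.** **1. Order of events, side by side**

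| Place | Order |
|---|---|
| XIV Procedure | consent, division, baseline tests, training |
| Participant timeline | consent, assessment, division |
| XVII schedule | screening, consent and baseline variables at enrolment, then allocation |

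Section XIV stands against the other two. The row labels in the schedule are unfilled template text, but the column marks are clear.

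**2. Planned size.** Section IX gives 28 per group and 10% dropout: 2 × 28 = 56, and 56 × 1.10 = 61.6, so 62, or m = 31 per arm. This step reproduces. The 28 does not follow from the printed formula, since 2 × 3.60² × 0.125² / 0.064² = 98.9. That is a separate matter, and nothing below depends on it.

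**3. Equal arms imply a restriction.** Unrestricted coin tossing of 62 players gives exactly 31:31 with probability C(62,31)/2^62 = 0.101. Guaranteed equality therefore needs a fixed pool, an arm that closes when full, or a similar rule. The protocol names none.

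**4. Assignments certain in advance, if past assignments are visible**

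- *One batch draw:* 0.
- *One by one from a shuffled pool of 31 + 31:* expected 2m/(m + 1) = 62/32 = 1.94. The last is always known; there is a 49% chance of 2 or more and 24% of 3 or more.
- *One by one, coin toss until an arm reaches 31:* expected 2m × C(2m,m)/2^(2m) = 62 × 0.1009 = 6.26. In 40,000 simulated sequences the mean was 6.26, the median 6, and the 10th to 90th percentiles 1 to 12.

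With m = 28 the two sequential figures are 1.93 and 5.94, so they depend little on the exact size.

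**5. Would small blocks help?** Take the rate of correct guesses when one always guesses the under-filled arm. For one pool or block of 2m, the expected number correct is m + 0.5 × (4^m/C(2m,m) − 1).

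- Pool of 62: 31 + 0.5 × (9.91 − 1) = 35.45, or 57%.
- Block of 6: 3 + 0.5 × (64/20 − 1) = 4.10, or 68.3%.
- Block of 4: 2 + 0.5 × (16/6 − 1) = 2.83, or 70.8%.

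Mixing blocks of 4 and 6 gives about 69%. Because staff see past assignments, small blocks raise predictability overall.

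**The case against.** The strongest reply is that nothing says players enter one by one. Section XIV takes consent from all participants and then divides them, which reads naturally as one batch, and under a batch draw no assignment is predictable. The one-year duration covers the whole study and does not show rolling assignment. This stands, so predictability can be raised only conditionally.

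A reader might go further and infer that the last assignments are known in advance and that steering would bias the result by a stated share of the planned effect. Suppose the certain players are steered by k = 0.25, 0.5 or 1 times the planning SD of 0.125 s. Then (6.26/31) × k × 0.125 s is 10%, 20% or 39% of 0.064 s. The documents do not support that claim, for three reasons. The values of k are invented. The close-when-full rule appears nowhere; the fixed pool gives (1.94/31) × k × 0.125 s, or 3%, 6% or 12%, and a batch draw gives 0. The scales also differ: 0.064 s is a pre-to-post change, while steering shifts a player's level, which would largely cancel if changes are compared.

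A reader might also infer that "Simple random sampling" sets a coin-toss assignment that conflicts with equal arms. It does not; it is listed as the sampling technique.

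Two further defences carry some weight. Assessment in the participant timeline could mean eligibility only, although the section XVII schedule still puts baseline before allocation. The CONSORT chart is not shown and front pages are missing, so concealment may be described there.

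**Conclusion.** The point holds in limited form. The order of baseline testing and division is contradictory on the face of the protocol, and that needs no assumption. The visible text also describes no concealment while requiring equal arms by an unnamed restriction. Under section XIV as written, staff would take the baseline timings knowing the arm; this rests on staff being unblinded, as the text implies by naming participants only.

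Predictable final assignments follow only if entry is one by one and past assignments are visible: on average about 2 of 62 with a fixed pool, about 6 with an arm closed when full, and at least 1 in either case. Those counts do not cap the risk, because without concealment any assignment may be foreseen or altered. No size of bias can be derived from the documents. The change is worth making because it is cheap and cannot be made later.

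**What to change.** Reconcile section XIV with the participant timeline and the section XVII schedule, so that an assignment is released only after consent, eligibility and baseline results are recorded. Then state one of two procedures.

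- **Preferred, batch entry:** one computer-generated 31:31 draw after the last baseline test, or one draw per recruitment batch once every player in that batch has been tested. It is run by a college staff member who does not screen, train or test players.
- **One-by-one entry:** a computer-generated list held by that same person and released through sequentially numbered, sealed, opaque envelopes. Avoid small blocks, because past assignments are visible, and change the requirement from equal to approximately equal arms.

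The cost is a short amendment and, for the second option, a set of envelopes. No extra players or tests are needed. Arms may end slightly unequal. Even under wholly unrestricted assignment the SD of an arm's size is √62/2 = 3.9, so a one-SD imbalance is about 35 against 27. The variance of the group difference then rises by (1/35 + 1/27)/(2/31) − 1 = 1.7%. The change does not blind the post-training tests.

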## XV. CONSORT FLOW CHART

[figure not shown]

### Participant timeline:

Once ethical approval is obtained from the university ethical committee, the subjects will be recruited from the RNPC Department of Sports Physiotherapy. After receiving consent from the subjects, they will be assessed and then will be divided into 2 groups.

### Group A:

Accentuated eccentric loading Countermovement jump, drop jumps with Ladder training

| Exercise category                                         | Procedure:                                                                                                                                                                                                                                                                                                                            | Reps/sets and duration                                                                                           | Progression                                                                                                                                |
|-----------------------------------------------------------|---------------------------------------------------------------------------------------------------------------------------------------------------------------------------------------------------------------------------------------------------------------------------------------------------------------------------------------|------------------------------------------------------------------------------------------------------------------|--------------------------------------------------------------------------------------------------------------------------------------------|
| Accentuated eccentric loading (ael) countermovement jumps | 

- use dumbbells or a weighted harness for eccentric loading.

- perform countermovement to approximately 90° knee flexion.

- drop the load before the concentric phase for maximal jump.

                                                                               | Weeks 1-3: 4 sets of 8 repetitions
weeks 3-6: 4 sets of 10 repetitions
(3 sessions per week) | Start with 10-20% of body mass as additional eccentric load, progressively increasing based on tolerance. Rest: 2 minutes between sets.    |
| Drop jump training                                        | Procedure: 

- step off the box without jumping.

- land softly on the balls of the feet and immediately perform a vertical jump.

                                                                                                                                         | Weeks 1-3: 4 sets of 8 repetitions
weeks 3-6: 4 sets of 10 repetitions
(3 sessions per week) | Drop height: begin with 30 cm, progressing to 50 cm as tolerated. Rest: 2 minutes between sets.                                            |
| Ladder training                                           | Drills: 

- weeks 1-2: straight run, hopscotch, single-foot hops zigzag pattern.

- weeks 3-4: two-foot run, backward hopscotch, single-foot lateral in/out hops.

- weeks 5-6: bunny hops, hopscotch variation, two-foot hops zigzag pattern

 | 6 repetitions of each drill x 2 sets per session.
(3 sessions per week)                                       | Rest: 30 seconds between repetitions, 60 seconds between sets. Focus on quick ground contact, coordination, and multidirectional movement. |

**Group B:** control group

| Exercise category      | Procedure:                                                                                                                                                                                                                                                                                  | Reps/sets and duration                                                         | Progression                                                                                                                                              |
|------------------------|---------------------------------------------------------------------------------------------------------------------------------------------------------------------------------------------------------------------------------------------------------------------------------------------|--------------------------------------------------------------------------------|----------------------------------------------------------------------------------------------------------------------------------------------------------|
| Ladder training | Drills:

- Weeks 1-2: straight run, hopscotch, single-foot hops zigzag pattern.

- Weeks 3-4: two-foot run, backward hopscotch, single-foot lateral in/out hops.

- Weeks 5-6: bunny hops, hopscotch variation, two-foot hops zigzag pattern. | 6 repetitions of each drill × 2 sets per session.

(3 sessions per week) | Rest: 30 seconds between repetitions, 60 seconds between sets.

Focus on quick ground contact, coordination, and multidirectional movement. |

**XVI. Outcome measures:**

**Primary outcome measure**

- **30 M Sprint Test-**

this study investigates the validity and reliability of various timing systems used in a 30-meter sprint test, focusing on their precision in performance evaluation. The systems analyzed include manual stopwatch timing.

Key findings:

- Manual timing: icc ranged from 0.60 to 0.75, showing moderate reliability but significant errors due to human reaction times.

The study concludes that fully automated systems are the most accurate and reliable for sprint performance measurement, ensuring consistency and reducing errors. These findings are crucial for sports performance testing, enabling coaches and researchers to make informed decisions about timing methods.

- **Agility T-Test-**

The agility t-test assesses an athlete's ability to accelerate, decelerate, and change direction quickly while maintaining control. It consists of a series of movements: sprinting forward, shuffling laterally, and backpedalling, typically completed in under 9.5 seconds for men and 10.5 seconds for women to be considered excellent. The test evaluates leg speed, power, and agility, making it a reliable measure for athletic performance across various sports. While it primarily measures change of direction, it also reflects overall athleticism and movement efficiency.

The test-retest reliability of the agility t-test is generally considered high. A study indicated an intraclass correlation coefficient (icc) of 0.84, suggesting that the test yields consistent results across multiple trial

## **XVII. Data collection, management, and analysis**

### **1. Data collection methods**

Pre-intervention data will be collected upon enrolment; additional post-intervention data will be collected after 6 weeks of the intervention.

|                                    |           | Study period |                                                                                      |       |       |       |       |       |           |
|------------------------------------|-----------|--------------|--------------------------------------------------------------------------------------|-------|-------|-------|-------|-------|-----------|
|                                    | Enrolment | Allocation   | Post-allocation                                                                      |       |       |       |       |       | Close-out |
| Timepoint**                        | $-t_1$    | 0            | $T_1$                                                                                | $T_2$ | $T_3$ | $T_4$ | $T_5$ | $T_6$ | $T_x$     |
| Enrolment:                  |           |              |                                                                                      |       |       |       |       |       |           |
| Eligibility screen                 | X         |              |                                                                                      |       |       |       |       |       |           |
| Informed consent                   | X         |              |                                                                                      |       |       |       |       |       |           |
| [list other procedures]     | X         |              |                                                                                      |       |       |       |       |       |           |
| Allocation                         |           | X            |                                                                                      |       |       |       |       |       |           |
| Interventions:              |           |              |                                                                                      |       |       |       |       |       |           |
| [intervention a]            |           |              | [figure not shown] |       |       |       |       |       |           |
| [intervention b]            |           |              | [figure not shown] |       |       |       |       |       |           |
| [list other study groups]   |           |              |                                                                                      |       |       |       |       |       |           |
| Assessments:                |           |              |                                                                                      |       |       |       |       |       |           |
| [list baseline variables]   | X         |              |                                                                                      |       |       |       |       |       |           |
| [list outcome variables]    |           |              | X                                                                                    |       | X     |       | X     |       | X         |
| [list other data variables] |           |              | X                                                                                    |       | X     |       | X     |       | X         |

## 2. Data management

Collected information will be summarized using basic descriptive statistics, including frequency percentages for qualitative data and mean with standard deviation for quantitative data.

### **3. Statistical method**

The complete analysis data set will include all the participants in the study with no missing values for all the parameters in the data set. The participants will be the subjects fulfilling the inclusion and exclusion criteria.

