**Minimum sample size required**

$$N1 = n2 = 2 \times [(1.96 + 1.64)^2 \times (0.125)^2] / (0.064)^2 = 28 \text{ per group.}$$

Considering a 10% dropout rate:

- Dropout = 10%
- **Total sample size required = 62.**

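### The only analysis set keeps players with no missing value on any parameter, so measured outcomes are discarded and randomised players excluded, with possible bias of unknown direction

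*Protocol*

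**What the plan says.** Section XVII.3 (Statistical method) states that the complete analysis data set will "include all the participants in the study with no missing values for all the parameters in the data set". It adds: "The participants will be the subjects fulfilling the inclusion and exclusion criteria". No other part of the protocol defines an analysis set, states that players are analysed as randomised, or says what happens to missing values.

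The sample size section has the step "Considering a 10% dropout rate" and ends with "Total sample size required = 62". Section XVII.1 places one follow-up measurement at the end of training: "additional post-intervention data will be collected after 6 weeks of the intervention". Annexure II records the 30 m sprint and the agility T-test on one sheet, each with a pre and a post value. Both tests are listed as primary outcomes.

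The treatment tables give both groups the same ladder training. Group A adds loaded countermovement jumps and drop jumps.

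**The concern.** The rule asks for completeness across all parameters, not completeness on the outcome being analysed. It therefore has two effects.

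- **Measured data are thrown away.** A player with both sprint times but no post-training T-test leaves the sprint analysis as well. The same holds the other way round.
- **Randomised players leave the comparison.** Anyone without a post-test is excluded, and the protocol itself expects some such players.

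Deletion after randomisation is harmless to the comparison only if loss is unrelated to outcome, or acts alike in both groups. Group A's programme is the longer and more demanding one, so unequal loss is plausible. If those lost also differ in sprint time from those who stay, the two groups of completers no longer differ by training alone.

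**Working it through.** **Inputs from the protocol.** Total 62 with "Allocation ratio: 1:1", so 31 per group; 10% dropout; target difference 0.064 s; "Pooled standard deviation = 0.125" (seconds).

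**The plan's own dropout step.** The stated 28 per group gives 56. Then 56 × 1.10 = 61.6, rounded up to 62, which reproduces the total. Expected loss is 0.10 × 62 = 6.2, about 6 players, leaving about 56. (The 28 itself does not follow from the printed formula: 2 × 3.60² × 0.125² / 0.064² = 98.9. That is a separate matter, and this point does not depend on it.)

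**Possible bias.** Let p be the share lost in a group and d the mean of those lost minus the mean of those who stay. Deletion moves that group's mean by −p × d, so the A minus B difference moves by −(pA × dA − pB × dB). With the same d in both groups this is −(pA − pB) × d. The protocol gives neither p by group nor d, so the values below are assumed.

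| Assumed loss | pA − pB | Size of d | Shift in difference | Share of 0.064 s |
|---|---|---|---|---|
| 5 of 31 in A, 1 of 31 in B | 4/31 = 0.129 | 0.5 SD = 0.0625 s | 0.008 s | 13% |
| 5 of 31 in A, 1 of 31 in B | 0.129 | 1 SD = 0.125 s | 0.016 s | 25% |
| 6 of 31 in A, none in B (extreme) | 6/31 = 0.194 | 0.5 SD | 0.012 s | 19% |
| 6 of 31 in A, none in B (extreme) | 0.194 | 1 SD | 0.024 s | 38% |
| Any split | any | 0 | 0 | 0% |

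A lower time is better. If those lost are slower than those who stay, the shift favours Group A. If they are faster, the same shift goes against Group A.

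For the extreme split, a two-sample t-test of 25 against 31 players was simulated with no true effect (20,000 runs, two-sided 5% level). It rejected in about 6.5% of trials at 0.5 SD and 10.9% at 1 SD. With loss unrelated to outcome it rejected in 5.3%, close to nominal.

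**Extra exclusions from the all-parameters rule.** Suppose each post-test is missing in 10% of players.

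- Both always missed together: 10% are excluded, about 56 of 62 analysed. The rule adds nothing to the planned loss.
- Missed independently: 1 − 0.9² = 0.19 are excluded. Then 62 × 0.81 = 50.2, so about 50 are analysed for each outcome, against 62 × 0.90 = 55.8, about 56, if each outcome used its own measured players.

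**The case against.** The strongest defence has four parts.

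1. **The direction of bias is not known.** A reader might infer that the rule makes Group A look better, through loss to soreness or injury. The documents do not support that: they give no dropout by group, no reasons for loss, and no link between loss and sprint time. Loss of faster players would act against Group A. This objection stands.

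2. **The power loss is mostly planned for.** The step from 56 to 62 already allows for whole players lost at 10%. A reader might also take 19% as the expected exclusion. It is not: both tests belong to one post-training collection on one sheet, so a player who drops out normally misses both and the figure stays near 10%. This stands too. Only players measured on one outcome but not the other add to the planned loss.

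3. **It is not an adherence rule.** A poor attender who is tested before and after stays in, and nothing moves players between groups. This is correct, so the rule should not be described as a per-protocol analysis by attendance. Nor does the eligibility sentence clearly remove players after randomisation; it may only describe who is enrolled. Exclusion for a blank descriptive field depends on the widest reading of an undefined term.

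4. **The wording may be loose, or a separate analysis plan may refine it.** The phrase may have been meant as a full analysis set. As written it says the opposite, and nothing else in the protocol corrects it. This is a stated rule and not a detail left open, so an unseen plan does not cure it.

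**Conclusion.** The point holds as a fault in a stated rule. The protocol fixes listwise deletion across all parameters as its only analysis set, while expecting about 6 of 62 players to drop out. Discarding a measured sprint time because the T-test is missing has no benefit, and excluding every randomised player without a post-test leaves the comparison open to bias.

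The size is conditional. Under the assumed 5 against 1 split and a 0.5 to 1 SD difference, the shift is 0.008 to 0.016 s in either direction, 13 to 25% of the target. It is zero if loss is unrelated to outcome. Extra loss of players beyond the planned 10% ranges from none to a total of 19% under the two missingness patterns shown. It should be corrected before data are analysed, since a choice of analysis set made afterwards would be open to challenge.

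**What to change.** Replace the sentence in section XVII.3 by: *All randomised players are analysed in the group to which they were allocated. Each outcome uses every player with that outcome measured.*

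Then add:

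- Seek the week-6 measurement also from players who stop training, where the investigator judges testing suitable. This matters most, because the new wording alone does not recover a player who has no post-test.
- Report the number of missing values and the reasons, by group and outcome.
- Keep the all-parameters complete-case result as a sensitivity analysis.
- If values are imputed, add a sensitivity analysis in which missing week-6 values are assumed worse in Group A. Imputation from baseline and group alone assumes that loss does not depend on the unseen result, so it does not address outcome-dependent loss.

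The cost is a few sentences in the statistical section, a little more analysis work, and a test visit offered to the few players who stop training.
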